## Discussion

Sexual problems, such as dyspareunia, vaginal dryness and a decrease of sexual satisfaction and desire, are frequently reported by GC survivors after treatment with RT, and occur in particular after combined EBRT+BT. Previous studies have shown that psychosexual support after treatment for GC should include cognitive behavioural interventions to increase dilator compliance and improve sexual functioning [2, 15, 20–26]. Furthermore, including the patient’s partner, if available, is preferred [26]. Therefore, we developed a nurse-led sexual rehabilitation intervention, including these key components, to support sexual improvement and vaginal dilator use after RT. This RCT will provide evidence about the efficacy of this nurse-led sexual rehabilitation intervention in terms of sexual functioning as measured by the FSFI [36], as well as evidence on other sexual outcome measures, compliance with vaginal dilation and the cost-effectiveness of the rehabilitation intervention. We expect that women who received the intervention will report a statistically significantly greater improvement in sexual functioning and – for women who receive EBRT+BT – higher compliance with dilator use, from baseline to 12 months post-RT than women who receive optimal CAU. If proven effective, the rehabilitation intervention will be a valuable addition to the care offered to GC survivors and will contribute to improved quality of life after GC.

The SPARC study has several notable strengths, including the randomized trial design, the multicentre nature (with participation of all Dutch GC centres), the comparison of the intervention group with a control group, the use of a clear treatment protocol and training protocol, the use of intention-to-treat analyses and the long-term follow-up assessments of outcomes. This trial also has several limitations. First, even though the FSFI is one of the most widely used questionnaires to measure sexual functioning among female cancer survivors, it produces biased results for women who have not been sexually active in the past month [36, 58]. The majority of the questions (15 out of 19) include a response option of ‘No sexual activity’ or ‘Did not attempt intercourse’, scored as zero. This is problematic because lower scores indicate more severe dysfunction whereas not engaging in sexual activity during four weeks does not necessarily imply sexual dysfunction. Sexual inactivity could have multiple reasons, such as the absence of a partner. As our study sample consists of partnered as well as unpartnered women, we chose to randomize participants stratified by having a partner. Second, despite the proposed benefits of regular dilator use (i.e., preventing or minimising vaginal stenosis), unequivocal evidence for its effectiveness in reducing vaginal complaints and better sexual functioning is still limited. The consequences of stenosis remain individually determined, with some women unaffected by significant vaginal complaints, while others experience long-lasting sexual problems [11]. However, because dilator use aims to prevent or minimise stenosis, we expect that this could positively affect vaginal complaints and sexual functioning indirectly. Therefore, we will include dilator use as a mediator instead of an outcome measure in the statistical analyses. Third, because RT-induced sexual problems develop soon after treatment, we start evaluating GC survivors early in the recovery phase and continue until 12 months post-RT. A longitudinal study that analysed functioning and symptom scores for quality of life of cervical cancer patients who underwent EBRT+BT demonstrated that RT-induced sexual problems increased to a clinically relevant degree in the first three months, after which it stayed elevated, even after 12 months [59]. This study did not include a sexual rehabilitation intervention. By offering a nurse-led sexual rehabilitation intervention we hope to find significant greater improvement in sexual functioning between the intervention- and optimal CAU control group at 12 months follow-up. However, it is possible that sexual functioning among GC survivors might improve further after 12 months post-RT. Therefore, we intend to plan an additional long-term follow-up measure at 24 months post-RT. Fourth, the possibility of contamination of our optimal CAU control group exists. In the past few years, the Dutch CAU regarding sexual problems after RT improved and was aligned nationwide, possibly as a consequence of the findings of our pilot study [32]. This resulted in fewer differences between the participating centres in the current trial, as all participating women are offered an information session, information booklet and a dilator set (if applicable) post-RT free of charge. In the current study, this improved CAU, combined with the possibility that the specialized trained nurses also come into contact with the control group, may result in the control group receiving better post-RT psychosexual care than intended - as the nurses might find it difficult not to use the additional trained skills to help these patients. This well-known problem of contamination within individually randomized intervention studies could be avoided by cluster randomization (i.e., on centre level instead of patient level). However, this method also introduces other potential threats to internal validity, as the number of centres in our study is limited and only a part of the centres could be randomized (n = 8, as a consequence of the training that was already completed in two centres for the pilot study) [32]. Because of the specific variation in the patient population, RT treatment procedures and follow-up procedures across centres, we decided to randomize on patient level, with the risk of contamination. During their training, the nurses received clear instructions on the procedure to be followed in both study groups and about the contamination risks.

The importance of the availability of a sexual rehabilitation intervention is evident from the British [60], Australian [61] and Dutch guidelines [62] which state that more attention has to be paid to sexual functioning after RT for GC. To our knowledge, this is the first RCT evaluating the (cost-)effectiveness of a nurse-led sexual rehabilitation intervention in improving sexual functioning and dilator use compliance of GC patients after RT. If proven to be effective, the intervention will be a valuable addition to GC survivors’ standard care. It will ultimately improve the quality of life of patients (and their partners). The intervention can be implemented nationwide directly after study completion, as all end-users were involved in the preparatory studies [17, 18, 32] and nurses in all Dutch GC centres are trained in the treatment protocol. Implementation is further enhanced by the relatively low costs of personnel and materials. In addition, if successful, the intervention could be extrapolated to women with other types of pelvic cancer (e.g., rectal cancer, anal cancer and bladder cancer).

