It can be concluded that psychosexual support after treatment for GC should include motivational issues and psychosexual interventions to increase dilator compliance and improve sexual functioning. Furthermore, involvement of the partner is preferred. There is a need for a condensed, practical and (cost-)effective sexual rehabilitation intervention, consisting of psycho-education combined with elements of psychosexual-based cognitive behavioural therapy for GC patients and their partners after RT [27–31]. Therefore, based on the results of our previous studies [17, 18, 21], we developed a nurse-led sexual rehabilitation intervention to support sexual improvement and vaginal dilator use after RT. The intervention has multiple aims: motivating women, giving tailored advice, strengthening self-management, promoting couples’ mutual coping and support processes and, for women who received EBRT+BT, providing information and coaching on use of vaginal dilators on a regular basis. The results of our pilot study regarding the feasibility of the intervention demonstrated that this intervention improved women’s sexual functioning and that it supported them in their dilator use [32]. Furthermore, the nurses who were trained and supervised to guide the intervention felt capable to support the women.

In this manuscript we present the design of the SPARC (Sexual rehabilitation Programme After Radiotherapy for gynaecological Cancer) study, a multicentre randomized controlled trial (RCT) which evaluates the (cost-)effectiveness of the nurse-led sexual rehabilitation intervention in improving sexual functioning and dilator use of GC patients after RT. Participants are randomized to either the intervention- or optimal care as usual (CAU) control group (1:1). We expect that women who receive the intervention will report a statistically significant greater improvement in sexual functioning and – for women who receive EBRT+BT – higher compliance with dilator use, from baseline to 12 months post-RT than women who receive CAU.

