### Study groups

One month after completion of RT, women in both study groups receive an information booklet. The information booklets, which contain specific information to improve knowledge and coping strategies regarding sexual rehabilitation after either EBRT+BT or EBRT only, are based on the booklet developed in the pilot study [32]. The booklets are provided in both a printed and online version. Women in both study groups who received EBRT+BT are given a dilator set and are advised to start vaginal dilation for 1 to 3 min, 2 to 3 times a week around 4 weeks after RT when the vagina is sufficiently healed [11, 18].

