CAU = Care as usual; CEQ = Credibility/Expectancy Questionnaire; EORTC QLQ-C30 = European Organization for Research and Treatment of Cancer Quality of Life Questionnaire-Core 30; EORTC QLQ-CX24 = European Organization for Research and Treatment of Cancer Quality of Life Questionnaire-Gynaecological Cancer Module; EORTC QLQ-EN24 = European Organization for Research and Treatment of Cancer Quality of Life Questionnaire-Endometrial Cancer Module; EQ-5D-5 L = EuroQol 5D-5 L; FSDS = Female Sexual Distress Scale; FSFI = Female Sexual Function Index; FSQ = Fear of Sexuality Questionnaire; HADS = Hospital Anxiety and Depression Scale; IES = Impact of Event Scale; MMQ = Maudsley Marital Questionnaire; QoL = Quality of Life

Additionally, the secondary outcome measures include a 4-item questionnaire for women treated with EBRT+BT regarding the frequency of dilator use: (1) ‘How often have you used the dilator in the past month?’, (2) ‘Which size(s) dilator(s) did you use?’, (3) ‘How often did you have other kinds of penetration (including penile penetration) in the past month?’, and (4) ‘How often did you use petroleum jelly (Vaseline) tampons?’.

Furthermore, the following vaginal symptoms are assessed by standardized clinical examination for all participants: dryness, shortening/tightening, mucositis, discharge, blood loss, fibrosis, atrophy, pain, length (in millimetre) and dyspareunia. Vaginal symptoms will be recorded using the Common Terminology Criteria Sexual rehabilitation after RT for gynaecological cancers for Adverse Events (CTCAE), version 4.037.

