### Statistical analysis

T-tests or appropriate non-parametric statistics for independent samples will be used to evaluate the comparability of the intervention and control group at baseline in terms of sociodemographic and clinical characteristics. If, despite the stratified randomization procedure, the groups are not comparable on one or more background variables, those variables will be employed routinely as covariates in subsequent analyses.

Questionnaire scores will be calculated according to published scoring algorithms. Differences in changes in the primary outcome measure and secondary outcome measures between groups (intervention vs. control group) over time (T1-T5) will be evaluated using multilevel models and are based on an intention-to-treat approach. Effect sizes will be calculated using standard statistical procedures.

Furthermore, multilevel models will be used to investigate if improvement in sexual functioning in the intervention group is moderated by treatment/cancer characteristics and patient characteristics or mediated by e.g. sexual symptoms and vaginal symptoms or frequency of dilator use. Cost-effectiveness will be analysed using net benefit analysis, with multiple imputation to account for missing data.

Per protocol analyses will also be carried out (as a secondary analysis), comparing women who meet minimal compliance levels with the intervention with the control group. We will use correlation analyses to examine the relationship between degree of intervention adherence and intervention effect.

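### Dilator use is a stated hypothesis and a listed secondary outcome, yet the Discussion says it is analysed as a mediator and not as an outcome; the roles must be reconciled before analysis

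*Protocol article*

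**What the plan says.** **Hypothesis.** The Abstract, the Background and the Discussion each state two expectations in one sentence: greater improvement in sexual functioning and, for EBRT+BT women, "higher compliance with dilator use, from baseline to 12 months post-RT than women who receive CAU". The Discussion repeats it almost word for word: "higher compliance with dilator use, from baseline to 12 months post-RT than women who receive optimal CAU".

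**Promised evidence.** The opening paragraph of the Discussion lists, among the things the trial will inform, "compliance with vaginal dilation and the cost-effectiveness of the rehabilitation intervention". Its closing paragraph again describes the trial as evaluating effectiveness for dilator compliance.

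**Outcome status.** In Outcome measures, after Table 2: "the secondary outcome measures include a 4-item questionnaire for women treated with EBRT+BT regarding the frequency of dilator use".

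**Analysis.** The Statistical analysis section gives a general rule, "Differences in changes in the primary outcome measure and secondary outcome measures between groups (intervention vs. control group) over time (T1-T5", to be evaluated with multilevel models by intention to treat. It names dilator use only once, in the list of factors by which improvement in sexual functioning may be "mediated by e.g. sexual symptoms and vaginal symptoms or frequency of dilator use".

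**Exclusion.** The second limitation in the Discussion: "Therefore, we will include dilator use as a mediator instead of an outcome measure in the statistical analyses".

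**Timing.** Under Study groups, EBRT+BT women in both arms are "advised to start vaginal dilation for 1 to 3 min, 2 to 3 times a week around 4 weeks after RT".

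**The concern.** A variable can be both a secondary outcome and a mediator, and here that would be the natural choice. The Discussion sentence rules it out: it sets one role in place of the other. Whether the programme raises dilator use is one of the trial's two stated questions, and the intervention devotes an extra session and several modules to it.

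Two things are at stake. First, an analyst who follows the Discussion sentence has no planned randomised comparison with which to answer the compliance question. Second, while both readings stand in the same article, the choice can be made once the results are known. A favourable compliance result could then be challenged as post hoc, and an unfavourable one could be left out on the ground that dilator use was only a mediator.

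**Working it through.** The point is textual. No figure in the article bears on it: the power calculation rests on the FSFI alone. For the record, its attrition step reproduces (64 / (1 − 0.40) = 106.7, so 107 per group, 214 in total, taken up to 220) and is unaffected.

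**Step 1. Set the statements side by side.**

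| Place | Role given to dilator use or compliance |
|---|---|
| Abstract; Background; Discussion, first paragraph | Hypothesis: higher in the intervention arm, EBRT+BT women |
| Discussion, first and last paragraphs | Question the trial will inform |
| Outcome measures, after Table 2 | Secondary outcome |
| Statistical analysis, general rule | Compared between arms, by virtue of being a secondary outcome |
| Statistical analysis, mediation sentence | Possible mediator |
| Discussion, second limitation | Mediator, and explicitly not an outcome |

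The first five rows are compatible with one another. The last is incompatible with the third and fourth, and it removes the planned test of the first.

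**Step 2. Does the stated reason support the exclusion?** The Discussion argues that evidence for a benefit of dilator use on vaginal complaints and sexual functioning is limited, and that any effect on sexual functioning is expected to be indirect. That is a reason to study mediation. It is no reason to drop the between-arm comparison, because whether the programme increases dilator use does not depend on whether dilator use improves function.

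**Step 3. Can the general rule be applied to dilator use as worded?** The rule concerns differences in changes over T1 to T5.
- T1 is completed before randomisation (Data collection), and randomisation takes place before radiotherapy is completed (Recruitment and randomization).
- Dilation is advised from around 4 weeks after radiotherapy (Study groups).
- Of the outcome questionnaires, T1 holds only the FSFI and the FSDS (Outcome measures).

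There is therefore no T1 value of dilator use, and no change from T1 can be formed. Even if dilator use keeps its secondary-outcome status, the rule needs an adapted form for it: a comparison of post-radiotherapy values.

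**The case against.** **The hypothesis is tested after all.** Read together, the secondary-outcome listing and the general rule do give a randomised comparison by intention to treat, and they stand in the Methods, whereas the contrary sentence stands in a limitations paragraph. This holds as one of two readings. A reader might infer that the compliance hypothesis definitely goes untested; the article does not support that. But the general rule does not mention dilator use, while the Discussion sentence addresses it by name and removes it.

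**Mediation covers it.** A mediation model can estimate the path from arm to dilator use, so it would be wrong to say that such a model is silent on the intervention's effect. The article, however, presents mediation as a way to explain improvement in sexual functioning, not as the test of the compliance hypothesis.

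**The analysis plan may settle it.** Definitions and models may well be left to that document. This is not an omission, though: two positive statements in the same article conflict, and an analysis plan cannot agree with both.

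**The phrase about baseline is harmless.** In the hypothesis sentence the change word attaches to sexual functioning, while compliance is only to be higher, so the phrase may simply mark the study period. That is a fair reading, and on the hypothesis sentence the point is no more than a request for clarity. The mismatch with the T1 to T5 rule remains.

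**The trial is underpowered for compliance.** A reader might infer this too. The article gives no EBRT+BT share, and the only compliance rate it offers (75% failing to use dilators regularly, Background) comes from earlier patients, not from this optimised control arm. An outcome listed as secondary also needs no power statement. No power claim is made here.

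**Conclusion.** The contradiction stands. The article makes dilator use a hypothesis, a promised result and a secondary outcome, and then says that it will not be analysed as an outcome. If the Discussion sentence governs, one of the two stated hypotheses has no planned between-arm test; if the general rule governs, it has one. The article does not say which. Separately, dilator use has no T1 value, so a change from T1 cannot be analysed.

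The reach is limited to one secondary outcome in the EBRT+BT stratum. The primary endpoint, its sample size and its analysis are not affected. This should be fixed before the data are analysed, but it is not a fault that undermines the trial. The conclusion rests on the article's wording alone and needs no numerical assumption.

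**What to change.** 1. **Discussion, second limitation:** replace the words that deny outcome status, so that dilator use is included as a mediator in addition to its analysis as a secondary outcome.
2. **Statistical analysis:** state that frequency of dilator use is compared between the randomised arms in the EBRT+BT stratum over the post-radiotherapy assessments, with no change-from-baseline term. Keep mediation as a separate, exploratory analysis.
3. **Hypothesis sentences (Abstract, Background, Discussion):** make clear that the phrase about baseline refers to sexual functioning only.

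The definition of compliance, the main time point and the model can be left to the statistical analysis plan, provided they are fixed before the data are analysed. The definition needs thought, because the questionnaire also records other penetration and petroleum-jelly tampons. So does the time point: the Background gives 9–12 months as the generally recommended period of use, so past-month use at T5 falls at about its end.

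The other consistent course is to withdraw the compliance hypothesis and the secondary-outcome listing openly. That would give up a question for which the data are being collected anyway.

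The cost is wording only, with no added data collection, visits or participants.

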## Data Availability

All (Dutch) materials, such as information folders, will be available by the end of current study and publication of the results. Data containing potentially identifying or sensitive patient information are restricted according to European law (General Data Protection Regulation (GDPR)). The datasets generated and/or analysed during the current study are not available in a public repository, but are available upon reasonable request via [name].

## Abbreviations

BT: Brachytherapy
CAU: care as usual
CEA: cost-effectiveness analysis
CEQ: Credibility and Expectancy Questionnaire
CRF: Case Report Form
CTCAE: Common Terminology Criteria Sexual rehabilitation after RT for gynaecological cancers for Adverse Events
EBRT: external beam radiotherapy
EORTC QLQ-C30: European Organization for Research and Treatment of Cancer Quality of Life Questionnaire Core 30
EORTC QLQ-CX24: European Organization for Research and Treatment of Cancer Quality of Life Questionnaire-Gynaecological Cancer Module
EORTC QLQ-EN24: European Organization for Research and Treatment of Cancer Quality of Life Questionnaire-Endometrial Cancer Module
EQ-5D-5L: 5-level EuroQol-5D
EQ-VAS: EuroQol visual analogue scale
FIGO: Fédération Internationale de Gynécologie et d’Obstétrique
FSDS: Female Sexual Distress Scale
FSFI: Female Sexual Function Index
FSQ: Fear of Sexuality Questionnaire
GC: gynaecological cancer
HADS: Hospital Anxiety and Depression Scale
IES: Impact of Event Scale
min: minutes
MMQ: Maudsley Martial Questionnaire
PROM: patient-reported outcome measure
QALYs: quality-adjusted life years
RCI: Reliable Change Index
RCT: randomized controlled trial
RT: radiotherapy
SPARC: Sexual rehabilitation Programme After Radiotherapy for gynaecological Cancer
T1: baseline
T2: one month post-radiotherapy
T3: three months post-radiotherapy
T4: six months post-radiotherapy
T5: twelve months post-radiotherapy
WHO: World Health Organisation
